### Intervention

For the purposes of this project, it will be assumed that the evidence component of the PARiHS framework for the value of pharmacists’ intervention in the care of patients with diabetes, dyslipidemia, or hypertension is sufficiently optimized [7–13] and that pharmacists are aware of, and support, this evidence [18, 30].

External, task-focused facilitation [31], informed by an evaluation of contextual factors using the Alberta Context Tool (ACT), on-site observations, and participant interviews, will be applied to train community pharmacies to develop alternative team processes that enable a greater number of medication management services to be provided to patients with pre-specified chronic conditions [32]. Permissions to utilize the ACT have been received. This facilitation process will assist pharmacy team members in thinking through the change process and provide them with a set of skills to develop change strategies in the future. Facilitators will also serve as a liaison between management and front-line staff to implement potential organizational change processes to ensure alignment between expected service provision and the operational reality of pharmacy practice.

The facilitation process will begin with an evaluation of the contexts of all of the pharmacies using the ACT. Then, baseline rates of the completion of medication management services will be measured using pharmacy software. Facilitated discussions (i.e., participant interviews) will follow with pharmacy team members (managers, pharmacists, and technicians) to explore the scores of each of the dimensions on the ACT, and to develop strategies to address any barriers identified. All intervention pharmacy team members will also be asked to complete a facilitation evaluation survey.

From this, an alternative team process will be developed to provide pharmacy teams with guidelines for how more medication management services could be completed. These guidelines may include physical layout considerations, workflow improvements, patient identification strategies including case finding [26], task delegation from pharmacists to pharmacy technicians and assistants [33], and alignment of job description expectations between front-line staff and management.

### Control

Control pharmacies will also complete the ACT, and baseline rates of the completion of medication management services will be collected. However, investigators will not meet with staff from these locations to discuss the results of the ACT or provide any assistance with implementing medication management services. A number of recent changes affecting the practice of pharmacy in Alberta, including simplification of the application process for prescribing authorization [34] and the launch of programs by advocacy organizations to support applying pharmacists [35], the regulation of pharmacy technicians [14], and changes to generic drug pricing and allowable professional fees [36], have occurred. Therefore, the use of a concurrent control group aims to isolate the effect of the intervention on the outcomes of interest from these compounding factors.

### Outcomes

All outcomes measured will be analyzed at the cluster level.

#### Primary outcome

As a feasibility study, process evaluation will form the primary outcome [37]. Process evaluation will be evaluated using the comparative baseline results of the ACT [38–40] for both groups, transcriptions of interviews, field notes, and the facilitation evaluation surveys [41]. These surveys will be undertaken pre- and post-intervention and are designed to capture stakeholders’ expectations, and final thoughts, about the process. Field notes will be kept during site visits and all subsequent interactions with the intervention sites, with the intention of tracking the identified needs, and implementation of the facilitated intervention. Overall, these data are intended to detail the facilitated intervention development process to gain insight into the needs of community pharmacies, the acceptability and uptake of modifications made, and the willingness of pharmacies to participate.

#### Secondary outcomes

**Service provision** To gauge the effectiveness of the intervention in improving medication management service provision rates, secondary outcomes will include descriptive analysis of the change in the number of formal and documented services in the aforementioned chronic conditions provided 6 months before versus after the intervention between the two groups. While the definition of medication management services varies in the literature, for the purposes of this study, they are defined as those services currently eligible for remuneration under the Alberta Pharmacy Services Framework [42] and include the following:

 Comprehensive Annual Care Plan (CACP) Standard Medication Management Assessment (SMMA) Follow-ups to CACP/SMMA Assessment and adaptation of a prescription Patient assessment for prescription renewal Patient assessment in a medication-related emergency (emergency prescribing) Optional services (those that can only be provided by pharmacists with additional certifications):

○ Assessment and administration of medications by injection

○ Patient assessment for initiating medication therapy

For the purpose of this study, service counts will be limited to the provision of a CACP, SMMA, or follow-ups to CACP or SMMA.

A CACP is designed to meet the unique needs of patients with complex health issues [42]. According to the Alberta Health Pharmacy Services Framework, ‘complex needs’ are defined as patients having at least two of the pre-identified chronic conditions or patients with at least one pre-identified chronic condition and one pre-identified risk factor (see Table 1) [42]. A CACP includes the completion of a patient assessment and a best possible medication history. This information is then used to develop a specific care plan to identify and resolve existing or potential drug-related problems, mutually develop therapy goals, and to follow-up and monitor the progress on identified goals. All information contained within the CACP is formally documented and provided to the patient and any other health professionals involved in the patient’s care, as needed. Prior to conducting a CACP, informed consent from the patient must be obtained.

**Table 1 Tab1:** **Qualifying conditions and risk factors**

Conditions	Risk factors
Hypertension	Obesity
Diabetes mellitus	Addictions
Chronic obstructive pulmonary disease	Tobacco
Asthma	
Heart failure	
Ischaemic heart disease	

An SMMA is designed to meet the needs of patients who do not qualify for a CACP [42]. In particular, patients must have at least one of the pre-specified chronic conditions and be taking at least three different Schedule 1 (prescription) medications or insulin, have diabetes and be taking at least one Schedule 1 drug or insulin, or use a tobacco product daily and be willing to receive tobacco cessation services. Steps for completing and documenting a SMMA are the same as those for a CACP. Patients having either a CACP or SMMA completed are eligible for follow-up interactions as required and outlined in the care plan developed with the pharmacist [42].

### Identification of feasible patient care outcomes

With the ultimate goal of improving patient care, this study also aims to identify feasible clinical outcomes for collection and analysis, including changes in clinical measures specific to diabetes, hypertension, and dyslipidemia management as recorded on applicable patients’ follow-up documentation. Potential outcome measures may include, but are not limited to the following:

 Glycosylated hemoglobin (HbA1c) Fasting plasma glucose Systolic and diastolic blood pressure Low-density lipoprotein cholesterol (LDL-C) High-density lipoprotein cholesterol (HDL-C) Triglycerides Total cholesterol to HDL-C ratio

Pharmacy staff and management will be consulted to determine if additional outcomes can be reasonably collected and are relevant for clinical and/or administrative purposes.

### Description of participating pharmacies

To determine the generalizability of this study’s findings to other pharmacies within the chain and externally, descriptive data on the pharmacies will be identified and summarized, including location, prescription count, and staffing level. This data, along with service provision counts and clinical outcomes, will be utilized in the estimation of the intracluster correlation coefficient.

### Data collection

Process evaluation data will be collected over the course of the study. Results from the ACT will be collected at baseline and 6 months, as well as results from the facilitation evaluation surveys for intervention pharmacies. Interview data will be collected as they are conducted through the start-up phase of the intervention, and field notes will be collected continually as data collection for the primary outcome begins. All data will be stored securely at the University of Alberta Epidemiology Coordinating and Research (EPICORE) Centre.

Data on the change in the number of medication management services provided will be collected from pharmacy software programs located within the respective stores participating. Baseline numbers of medication management services provided will be counted back 6 months from the time of data collection (for example, if data collection begins May 1, 2014, pre-intervention data will be collected starting from November 1, 2013). Final data regarding the number of medication management services provided following the intervention will be collected for both intervention and control pharmacies for 6 months starting after the first set of in-person visits with the intervention pharmacies.

Data for the secondary clinical outcomes at baseline and 6 months will be collected at the same time as follow-up data for the primary outcome, for all patients receiving CACP or SMMA services. It is of key importance to note that pharmacist participants will not be asked to complete any data collection for the sole purposes of completion of the study. As the intention of this project is to improve the sustainability of clinical intervention provision by pharmacists, it is paramount that their actions herein are as close as possible to what they would be performing after the conclusion of the study. All clinical parameters will be reported by the pharmacies to the study investigators in aggregate form, without any patient identifying information. These values, and the frequency of their collection, will be analyzed descriptively to gauge whether potentially clinically meaningful changes can be reasonably assessed by this method.

### Statistical analysis

All analyses for the primary and secondary outcomes will be based on the intention to treat principle. Pharmacy information, such as average weekly prescription count or pharmacists with additional certifications, will be presented descriptively for the purpose of determining the generalizability of the findings across all pharmacies in Alberta.

Results from the interviews, field notes, and the facilitation evaluation surveys will be analyzed for the purposes of a formative evaluation of the process of implementation of the facilitated intervention using a grounded theory approach [43]. In the case of this project, grounded theory is intended to develop a theory for the process of implementation of the facilitated intervention within the pilot group of pharmacies. Data analysis will be an ongoing process, as the constant comparative analytic technique will be employed to generate theory and adapt to the needs of the pharmacies, as the intervention is implemented [43]. The process evaluation themes identified by Grant et al*.*[44] for cluster-randomized trials of complex interventions will form the basis of this analysis. Facilitators will also track their time spent interacting with sites and implementing agreed-upon changes, for the purpose of determining the feasibility of providing the service to a larger number of pharmacies for future implementation projects.

We will also include, as part of the feasibility analysis, estimation of the effect size for the difference in change in the number of clinical services provided before and after the intervention between intervention and control groups, along with confidence interval estimates. This information, along with the acceptability of the intervention by pharmacies and members of the pharmacy chain management team and mean amount of facilitator time required per intervention site, will enable us to determine whether scale-up of the intervention across the entire chain is feasible, and if the potential costs to employ a facilitator for this service is likely to be sufficiently offset by increased billing for clinical services from the organization’s perspective.

Where patients received initial and/or follow-up services over the course of the intervention period, counts of the number, and type of clinical outcomes documented will be presented, along with mean baseline and follow-up values for these parameters. Due to the low sample size of this study and the primary focus on process outcomes, hypothesis testing on these values will not be performed.

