### Sample size

For this feasibility study, a pre-determined sample size of ten pharmacies (five intervention and five control) was decided upon as this was felt to be manageable by a single volunteer facilitator, and within the budgetary restrictions of our funding. The enrollment of five intervention sites is believed to be sufficient to initially detect common systemic organizational changes that may be of benefit to the pharmacy chain as a whole, while also allowing for refinement of the facilitation process for subsequent scale-up efforts. As the first study of this type in community pharmacies, the intracluster correlation coefficient (ICC) is unknown. A cluster-randomized trial of community pharmacies in Saskatchewan, Canada, estimated an ICC of 0.0143 [45]; however, it must be noted that data utilized to determine this value originated from various types of pharmacies (i.e., department mass-merchandise, chain-franchise, independent) [46]. One would expect our study to identify a higher ICC than reported in previous work due to our utilization of a single pharmacy chain for this study.

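### The facilitator-cost versus billing comparison rests on a time log and a service count that are both narrower than the question asked, and the net direction of error is undetermined

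*Protocol article*

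**What the plan says.** The Statistical analysis section names the inputs to the scale-up judgement: a between-group effect estimate with a confidence interval, acceptability to pharmacies and chain management, and the "mean amount of facilitator time required per intervention site". From these the investigators will judge whether scale-up is feasible and, from the chain's point of view, "if the potential costs to employ a facilitator for this service is likely to be sufficiently offset by increased billing for clinical services".

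- **Cost.** The only measurement described is the facilitator's own log: "Facilitators will also track their time spent interacting with sites and implementing agreed-upon changes". Under Sample size, the ten-pharmacy total is justified partly as "manageable by a single volunteer facilitator".
- **Facilitator's work.** The Intervention section describes context evaluation with the ACT, on-site observation, interviews, and development of an alternative team process with guidelines. It adds: "Facilitators will also serve as a liaison between management and front-line staff".
- **Benefit.** The analysis is an "estimation of the effect size for the difference in change in the number of clinical services provided before and after the intervention", comparing the two groups. Under Secondary outcomes, medication management services are broadly set out: "they are defined as those services currently eligible for remuneration under the Alberta Pharmacy Services Framework". Eight types are listed. The same section then narrows the measurement: "service counts will be limited to the provision of a CACP, SMMA, or follow-ups to CACP or SMMA".

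**The concern.** The offset question concerns the full cost of an employed facilitator and the chain's billing for clinical services in general. Both inputs are described on a smaller scope.

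An employee is paid for preparation, desk work and travel as well as for contact with sites. Because the facilitator here is a volunteer, the article describes no other cost measure that would pick up unlogged hours.

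For billing, what matters to the chain is the net change. The Randomization section treats pharmacist time as a key barrier to patient care services, so extra care plans could come partly at the expense of other billable work. Equally, delegation to technicians and better workflow, both part of the intervention, could raise the other services as well. A count limited to the annual care plan (CACP), the standard assessment (SMMA) and their follow-ups cannot distinguish these cases.

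At stake is one of the considerations in the scale-up decision: whether the facilitator would pay for itself.

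**Working it through.** The article gives no cost, fee, wage or break-even figure, so there is none to reproduce. The check compares scopes and then works out the sign of the error.

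**1. Time log against described work**

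| Work in the Intervention section | Covered by the log's wording? |
|---|---|
| On-site observation, interviews | Yes, this is site contact |
| Liaison with management | Partly; its stated purpose is to implement organizational change |
| ACT evaluation and scoring | Not clearly; no actor is named |
| Drafting of team process and guidelines | Not clearly; it precedes agreement on any change, and no actor is named |
| Preparation, travel | Not mentioned, although site visits are part of the intervention |

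**2. Service types**

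- Listed: CACP, SMMA, follow-ups, adaptation, renewal, emergency prescribing, injection, initiating therapy = 8.
- Counted: 3. Uncounted: 8 − 3 = 5, and 5/8 = 62.5%.
- Two of the five uncounted types need additional certification. Among the six other types, 3/6 = 50% are uncounted.
- These are shares of types. Shares by volume or fee cannot be computed.

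**3. Sign of the error**

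Let B be the billing gain from counted services and C the cost implied by logged time. Let s be the share of true facilitator time that is logged, and d the change in uncounted billing as a fraction of B.

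- Estimated net = B − C
- True net = B(1 + d) − C/s
- Error = estimated − true = C(1/s − 1) − dB

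A positive error favours scale-up. The first term is zero or positive for any s ≤ 1. The second term takes either sign.

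Illustration only, with assumed B = 100 and C = 80:

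| s | d = −0.25 | d = 0 | d = +0.25 |
|---|---|---|---|
| 1.0 | +25 | 0 | −25 |
| 0.8 | +45 | +20 | −5 |

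For s = 0.8 and d = +0.25: 80 × (1/0.8 − 1) − 0.25 × 100 = 20 − 25 = −5. The error vanishes at d = C(1/s − 1)/B, which for s = 0.8 is 20/100 = 0.20. Under-logging alone therefore favours scale-up, but a modest rise in uncounted services cancels or reverses it.

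**The case against.** A reader might infer that both gaps push the same way and that the comparison is tilted toward scale-up. The documents do not support that. Taken at face value, leaving out five service types omits any gains in them and so works against scale-up. The sign reverses only under displacement, which the article neither states nor rules out. Two further features could also make scale-up look less favourable than it is. Sample size says the pilot allows the facilitation process to be refined, so some logged time may not recur. Data collection counts benefit over only six months, although the intervention aims to leave teams with lasting skills.

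It can also be said that observation, interviews and part of the liaison are within the log, that ACT scoring and guideline drafting are not expressly assigned to the facilitator, and that a condensed article may leave the contents of a time sheet to the full protocol. The scale-up sentence itself speaks broadly of facilitator time required. Finally, the offset is one consideration beside service change and acceptability, it has no threshold, and process evaluation is the primary outcome.

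Most of this stands, and it limits the point to one of scope. It does not remove it: the article does state what the log covers and which services are counted, and both are narrower than the offset question it poses.

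**Conclusion.** The mismatch of scope holds. On the cost side the direction of the omission is known: if the facilitator does off-site work that goes unlogged, cost is understated. This rests on reading the log's wording as written and on the facilitator doing at least some of that work. On the billing side the direction is unknown, so the net direction is undetermined.

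No size can be derived from the documents. Any multiplier for the cost-to-benefit ratio would rest on assumed shares of logged time and displaced billing that nothing in the article anchors; the figures in the table above show sign only. The billing offset should not be read as the sole progression criterion, and the primary process evaluation is unaffected. This is an inexpensive improvement to one input to the scale-up judgement.

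**What to change.** - **Time.** Log all facilitator time per intervention site by task: preparation, ACT and interview work, guideline development, management liaison, travel, site contact and implementation. Separate one-off development from recurring time, and use the total in the offset judgement.
- **Billing.** Keep the secondary outcome as CACP, SMMA and follow-ups. In the software extraction already planned for both arms, also pull before and after counts of the other five listed types. Base the offset on the intervention-minus-control net change in billing over all eight.
- **Fallback.** If the other types are not extracted, confine the billing conclusion to CACP, SMMA and follow-ups, and say so.

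The cost is a fuller time sheet for one facilitator, a few more billing codes, and a stated time per site that will look less favourable. Using the pharmacy software adds no study-only recording by pharmacists, which Data collection rules out. Trial status says the intervention is already under way, so the time sheet is the urgent part: unlogged hours are hard to reconstruct, whereas service counts can be drawn from the software afterwards.

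### The baseline and follow-up clinical means are not restricted to patients who have both values, so their difference mixes change with who returned

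*Protocol article*

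**What the plan says.** The last paragraph of the protocol article's Statistical analysis section defines who contributes: "Where patients received initial and/or follow-up services over the course of the intervention period". For those patients, "counts of the number, and type of clinical outcomes documented will be presented, along with mean baseline and follow-up values for these parameters". The same paragraph rules out hypothesis testing on these values.

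Four other statements bear on how the means will be formed.

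- **Population.** Data collection gathers the clinical values at baseline and 6 months "for all patients receiving CACP or SMMA services", so not only from those who come back.
- **Source.** Data collection also says that "pharmacist participants will not be asked to complete any data collection for the sole purposes of completion of the study". The values are whatever routine care happened to document.
- **Level.** "All clinical parameters will be reported by the pharmacies to the study investigators in aggregate form, without any patient identifying information".
- **Who is followed up.** The text after Table 1 says that patients with either type of care plan are "eligible for follow-up interactions as required and outlined in the care plan developed with the pharmacist".

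The purpose is given in Data collection: the values, and how often they were collected, are to be "analyzed descriptively to gauge whether potentially clinically meaningful changes can be reasonably assessed by this method". The section on identifying feasible patient care outcomes likewise describes the target as changes in clinical measures.

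**The concern.** The stated question is about change, but the planned summary is two separate means. As the inclusion rule is written, those means rest on different sets of patients wherever follow-up is incomplete. Incomplete follow-up is to be expected, because it depends on the care plan and on routine documentation.

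If the patients who return had different baseline values from those who do not, the comparison of means carries that difference along with any real change. Improvement in returning patients could be understated or hidden, or a change could appear where there is none. Because pharmacies send aggregates without identifiers, the investigators cannot pair the values later. The pairing has to be specified before the pharmacies tabulate.

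What is at stake is the feasibility judgement on clinical outcomes, which would inform the choice of measures for a scaled-up study.

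**Working it through.** The plan gives no SD, return rate, expected change or sample size for the clinical values, so there is no figure of its own to reproduce. The structure below comes from the documents. Every numerical input is an assumption.

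**Step 1. The identity.** Let d be the mean within-patient change in those with both values, s the share of the baseline mean contributed by initial-only patients, and b_both and b_init the mean baselines of the two groups. If no follow-up-only patients lack a baseline:

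difference of means = d + s × (b_both − b_init)

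The second term is pure composition. It vanishes if everyone returns (s = 0) or if the two groups start at the same level.

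**Step 2. Illustration in systolic pressure.** Assume SD 18 mmHg, d = −5 mmHg, a fraction p returning, and correlation r between the baseline value and an underlying normal tendency to return. The returning patients' baseline exceeds the mean of all initial patients by r × i(p) × SD, with i(p) = φ(z)/p. Here i(40%) = 0.966 and i(30%) = 1.159.

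| p | r | Baseline excess (mmHg) | Difference of means (mmHg) |
|---|---|---|---|
| 40% | 0 | 0 | −5.0 |
| 40% | 0.2 | 0.2 × 0.966 × 18 = 3.5 | −1.5 |
| 40% | 0.3 | 0.3 × 0.966 × 18 = 5.2 | +0.2 |
| 40% | 0.5 | 0.5 × 0.966 × 18 = 8.7 | +3.7 |
| 30% | 0.5 | 0.5 × 1.159 × 18 = 10.4 | +5.4 |

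At 40% returning, the sign changes when r × 0.966 × 18 exceeds 5, that is, r above 5/17.4 = 0.29. By the identity in step 1 with s = 0.6, this means a baseline gap between returning and non-returning patients of 5/0.6 = 8.3 mmHg.

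The bias can also run the other way. With r = −0.2 and 40% returning, a true change of zero reads −3.5.

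**Step 3. Illustration in HbA1c.** Assume 40 patients with both values, falling from 8.5 to 8.0 (d = −0.5).

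- 40 initial-only patients at 8.5: baseline mean 8.5, difference −0.50. No bias.
- 40 initial-only patients at 8.0: baseline mean 8.25, difference −0.25. Shrunk.
- 40 initial-only patients at 7.5: baseline mean 8.0, difference 0.00. Hidden.
- 60 initial-only patients at 7.5: baseline mean (40 × 8.5 + 60 × 7.5)/100 = 7.9, difference +0.10. Reversed.

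Reversal needs s above 0.5 divided by the baseline gap: above 50% for a gap of 1.0 point, above 33% for 1.5 points, and never for 0.5.

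**Step 4. Follow-up-only patients.** Those with no baseline value add a second term, t × (f_only − f_both), where t is their share of the follow-up mean and f_only and f_both are the mean follow-up values. For example, take the 40 initial-only patients at 7.5 and add 40 follow-up-only patients at 8.5. The follow-up mean becomes 8.25 against a baseline mean of 8.0, a difference of +0.25. If their earlier baseline is retrieved, they become paired patients and the term disappears.

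**The case against.** Five points can fairly be made for the plan.

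- **Denominators are not stated.** The inclusive clause may govern mainly the counts, with the means simply added. The section on feasible patient care outcomes speaks of values on patients' follow-up documentation, which could point to returning patients. This stands to the extent that the unpaired reading is not the only one. It is still the plain reading of the operative rule, and no sentence restricts the means.
- **An article condenses a fuller document.** Omitting an SD of change would be no finding in itself. What remains is a stated inclusion rule and a stated statistic which, with aggregate reporting, cannot be repaired afterwards.
- **Little rests on these means.** They are secondary and untested, the plan does not say they will be subtracted, and the scale-up criteria in Statistical analysis do not name them. This limits the consequence. It does not remove it, since the values are collected "to gauge whether potentially clinically meaningful changes can be reasonably assessed by this method". The planned counts would reveal sparse follow-up, but not whether returning patients differed at baseline.
- **Follow-up-only patients may have a baseline on file.** Follow-up presupposes an earlier care plan, so they add to the problem only if that earlier value is not retrieved. This stands. The initial-only patients suffice for the argument.
- **The remedy has limits.** If high-baseline patients return, their paired change is open to regression to the mean. A longer tabulation must also respect the rule against study-only data collection by pharmacists. Both stand, and the fix has to deal with them.

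A reader might infer that the planned means will show the wrong sign, or that sicker patients are the ones who return. The documents support neither. Follow-up according to the care plan makes selection plausible, but it does not establish that return depends on the marker's level, or in which direction.

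**Conclusion.** The point holds in a limited form. As written, the baseline and follow-up means are not confined to the same patients, so their difference is not a clean estimate of change. If return is related to the baseline value, the difference can be shrunk, exaggerated or, under stronger selection, reversed.

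The size is unknown, and the figures above only show what is possible. Under the systolic assumptions with 40% returning, a correlation of 0.2 removes 3.5 of the 5 mmHg without changing the sign; reversal needs about 0.29 or more. With no relation between baseline and return, there is no bias.

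The effect is confined to the exploratory aim of judging whether clinically meaningful change can be assessed from routine records. The primary process evaluation and the service counts are untouched. The change is worth making because it is cheap and cannot be made once only unpaired aggregates have been sent.

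**What to change.** Amend the last paragraph of Statistical analysis so that each pharmacy's aggregate report gives, for each marker:

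1. the number of patients with an initial value;
2. the number with both an initial and a later value, retrieving the earlier baseline of follow-up-only patients where it is on file;
3. in those with both values only, the mean baseline, the mean follow-up, and the mean and SD of the within-patient change;
4. the mean baseline of those without a follow-up value.

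Base any statement about change on item 3, and use item 4 to show how far returning patients differ from the rest. State that the paired result describes returning patients only and is open to regression to the mean, and present it beside the same figures from the control pharmacies. That comparison helps but is not a full correction, because intervention pharmacies are encouraged to use case finding and may bring in different patients.

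The cost is that fewer patients contribute to the change and the extract is slightly longer. It remains aggregate and unidentified and needs no new measurement. It should be drawn from existing records, so that pharmacists are not asked to collect anything for the study alone.
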